### Outcomes

In this exploratory study we will evaluate:How many service users are invited to complete the PHP (Reach)How many service users express an interest in taking up that offer (Reach)Which version of the PHP was used (i.e. paper vs digital)How many service users begin a PHP (Reach)How many PHPs are completed fully and breakdown of which items are completed/not completed (Efficacy)The time taken to complete the e-PHP (Efficacy) (measured automatically electronically)Whether the service user needed support from their care co-ordinator to complete the PHP (Efficacy)How many service users complete a repeated PHP (Maintenance)The change in uptake of physical health actions by service users between first and repeat PHPThe timescale of any actions taken will be determined using an audit of the Electronic Patient Journey System from the date that the PHP is completed.Patient activation levels using the Patient Activation Measure (PAM) [26]Staff confidence in working with physical health using the Physical Health Attitude Scale for mental health nurses (PHASe) [27]

Outcome data will be collected by one researcher (JW) depending on the version used as follows: the researcher will collect data from clinical staff on their caseload, who has been offered the PHP and who expressed an interest in using it, who began one and who completed it, and who needed support. The researcher will monitor which version of the PHP is used, how many people complete a repeated PHP, and change in uptake of physical health actions. The PAM will be completed when the initial PHP is completed, and the PHASe questionnaire will be completed when researcher starts working with each team.

Figure 3 shows the PHP study schedule of enrolment and assessments. As this is a QI study, this figure is different to traditional RCT schedules. The SPIRIT checklist can be found in Additional file 1.

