## Abstract

**Background:**

People with serious mental illness (SMI) have poorer physical health and reduced lifespans compared to the general population. Reasons for this are complex, but one important area is the identification and treatment of physical health conditions. In England, services are structured into primary and secondary care; physical and mental secondary health services are separate. This often leads to a lack of co-ordination of care, with people missing the screening and treatment they need. People with SMI may find accessing physical health services more difficult due to the impact of their symptoms and/or a lack of social support. When they do access physical care, there may be ‘diagnostic overshadowing’ where physical health concerns are put down to a mental health diagnosis. Creating tools to support people with SMI to assume more control of their physical health may help to ameliorate some of these problems. The aim of this study is to evaluate the use of a service user-held Physical health plan (PHP) for secondary mental health service users to determine whether its use increases uptake of physical health services.

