To date, there is little understanding of how people with SMI experience their physical health and the support they would like with it. The barriers to self-managing physical health identified by mental health service users include the debilitating nature of mental illness, having a poor understanding of physical health, the experience of stigma from medical staff, and social isolation [14]. Self-management can improve health outcomes in this cohort [15], and tools such as Wellness Recovery Action Plans (WRAP), which have been developed with resources to be completed by the individual for people to self-manage their mental health, can be helpful in supporting personal recovery in mental health [16].

The aim of this study is to address some of the gaps identified in how people with SMI manage their physical health. Specifically, we ask whether the use of a service user-completed Physical health plan (PHP) by people with SMI using community mental health services increases their autonomy and uptake of physical health services.

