##### Locations

The PHP is designed to be used by service users and could therefore be used in any location. We are piloting it in community mental health teams.

The PHP will be completed once and then repeated 4–6 months later.

Tailoring—we will use the pilot to find out if the use of the PHP is different for different people and how much support is required to complete it.

Modifications—we will monitor and describe any modifications that are required.

*Exploratory study of the use of the PHP*

We will undertake an exploratory study of the use of the PHP in two community mental health teams.

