#### Introduction of PHP to service users

Staff in each participating team will be asked to introduce the PHP to all of the people on their caseload and invite them to complete it. We will make it clear that this is not compulsory. For each person who completes a PHP, informed consent will be obtained. An iPad/tablet will be placed in the reception of each participating team, with paper versions also available, and service user encouraged to complete the PHP whilst waiting for their appointments. If a paper version is used, a copy will be kept by the service user and one given to their care co-ordinator if they agree to this, and this copy will be uploaded on ePJS. If the PHP is completed in the iPad, it will then be emailed to the service user and their care co-ordinator (with permission). For service users who do not have an email address, the care co-ordinator will print a copy for them and ideally give it to them in the appointment or send it to them by post. Where Healthlocker is available, a service user may choose to use the PHP on their smartphone.

If there are gaps in the completed PHP, the service user will be asked to develop an action plan, with support from their care co-ordinator if wanted. As part of the evaluation of the study, the contents of each action plan and progress made with the action plan will be recorded if the participant gives permission for this. Each action plan will be reviewed at 4 months when the PHP is repeated, and any actions taken will be recorded.

One of the researchers will work closely with each of the participating team throughout the exploratory study to provide support for any problems or challenges encountered by staff. These will be logged to ensure a record is kept (as this will inform our implementation analysis and the future implementability of the PHP), and any changes made to procedures also logged.

All trial data will be stored by the research team in locked cabinets and password-protected files, and confidentiality will be maintained at all times. The research team only will have access to the final trial dataset.

This exploratory study will last 6 months.

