### Analysis

#### Quantitative data

We will analyse the use of the PHP using the questions listed above and calculate numbers and percentages for each question. For the PAM and PHASe questionnaires, we will look at change in scores.

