## Discussion

The information from the exploratory study will help us to understand how people use the PHP, what aspects of it are helpful, and how it is best used and implemented in individual teams and by individual service users. This will therefore help us in designing a larger trial to evaluate effectiveness and to be able to roll out the PHP for use across the Trust and wider across the NHS. People with SMI are known to have poorer physical health than the general population. This has become more widely acknowledged in recent years, and how to address this is a key question [29] with action needed at different levels from societal to individual. The PHP is one method developed to address this. This study aims to evaluate a service user-completed Physical health plan to find out if using it will increase access to physical health services. It is important to understand how new initiatives work at team level to understand if they can be implemented at scale. The use of a Theory of Change and the RE-AIM framework will help us to do this. We will use QI methodologies which will allow us to modify or amend the procedures if this is considered helpful by participants. We will work closely with service users and clinical staff to understand how it is used. This will also allow us to understand if the PHP can be implemented on a larger scale and inform the design of a large scale definitive RCT.

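### The aim asks whether the PHP increases uptake, but an uncontrolled first-to-repeat change in people who repeat it, with records audited only from PHP completion, can describe uptake and not attribute it

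*Protocol article*

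**What the plan says.** **The aim.** The Abstract (Background) says the study is "to determine whether its use increases uptake of physical health services". The Abstract (Methods) gives the same question to the six-month pilot. The Background asks whether PHP use "increases their autonomy and uptake of physical health services". The Discussion says the study aims "to find out if using it will increase access to physical health services", although the same section leaves the evaluation of effectiveness to a larger trial.

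**The design.** Under Locations: "We will undertake an exploratory study of the use of the PHP in two community mental health teams". Under Introduction of PHP to service users, staff are asked to "introduce the PHP to all of the people on their caseload and invite them to complete it". No comparison team or control period is described.

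**The measure.** The uptake outcome (Outcomes) is the "change in uptake of physical health actions by service users between first and repeat" PHP. How many people complete a repeat PHP is a separate outcome, and no return rate is assumed. The timing of actions comes from an "audit of the Electronic Patient Journey System from the date that the PHP is completed". Progress on action plans, which are drawn up where the first PHP shows gaps, is reviewed at the repeat PHP.

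**The analysis.** Quantitative data: "calculate numbers and percentages for each question".

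**The concern.** The aim is causal, and the design has nothing to set the observed change against. Three features combine:

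- No group or period goes without the PHP.
- The change can be computed only in people who complete a second PHP, and they may be likelier to have acted.
- The audit yields no rate of checks before the PHP.

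The other outcomes do not fill the gap. The items labelled Efficacy under Outcomes measure completion, time taken and support needed. The PAM and PHASe measure patient activation and staff confidence. Action-plan progress does concern uptake, but it is uncontrolled and also tied to the repeat PHP.

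At stake is how the result will be read. Against the stated aim, a count of actions taken on gaps, or a rise among repeaters, would be taken as evidence that the PHP works. The study is meant to inform the design of a definitive RCT.

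**Working it through.** The article states no sample size, power, uptake rate or return rate, so there is no figure to reproduce. The illustrations below use assumed inputs. The interval comes from the article: 4–6 months under Procedure (The intervention), and 4 months under Introduction of PHP to service users.

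**1. Gaps that close with no PHP effect.** Let *p* be the assumed probability that a person has a given check within a year, at a constant rate. The share of baseline gaps closed by month *m* is 1 − (1 − *p*)^(*m*/12).

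| Assumed annual uptake *p* | by 4 months | by 6 months |
|---|---|---|
| 30% | 1 − 0.7^(1/3) = 11% | 1 − 0.7^(1/2) = 16% |
| 50% | 1 − 0.5^(1/3) = 21% | 1 − 0.5^(1/2) = 29% |
| 70% | 1 − 0.3^(1/3) = 33% | 1 − 0.3^(1/2) = 45% |

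These apply where the result is read as actions taken on gap items, as the Procedure and the action-plan review invite. They give people with a gap the average rate. If people differ in their tendency to attend, those with a gap have a lower rate and the true closure is smaller.

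**2. The same model for a whole-group percentage.** The Materials section's example item asks about a blood pressure check within the past year, which is a rolling window. Take *p* = 50% and 4 months:

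- No→Yes: no check in the 12 months before the first PHP (0.5), then at least one in the next 4 months (0.206). 0.5 × 0.206 = 10.3% of people.
- Yes→No: no check from month −8 to month +4 (0.5), and at least one from month −12 to month −8 (0.206). 0.5 × 0.206 = 10.3% of people.

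The net change is zero. On rolling items, recurrence of checks alone does not raise the whole-group percentage.

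**3. Selective return.** Suppose 30% of first-PHP completers truly act.

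- Actors return at 60%, others at 30%: 0.3 × 0.6 / (0.3 × 0.6 + 0.7 × 0.3) = 0.18/0.39 = 46% acting among returners.
- Actors return at 70%, others at 20%: 0.21 / (0.21 + 0.14) = 60%.

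**4. Bounds without a model of return.** If returners show uptake *u* = 40% and a share *r* returns, uptake among all first-PHP completers lies between *ru* (no non-returner acted) and *ru* + (1 − *r*) (all did):

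- *r* = 40%: 16–76%
- *r* = 60%: 24–64%
- *r* = 80%: 32–52%

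Nothing in the stated outcomes or audit separates steps 1 and 3 from a PHP effect.

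**The case against.** The strongest reply is that this is what an exploratory pilot looks like. The Abstract calls it a pilot QI study, the Design section places it in the exploratory phase of the MRC framework with a separate definitive phase to follow, and the Discussion leaves effectiveness to a larger trial. That stands: the lack of a comparator is a legitimate choice. It does not rescue the wording of the aim, because the Discussion restates the effect question in the same section.

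Two further points limit the criticism. The first PHP itself records past uptake, so there is a retrospective self-reported baseline; what is missing is a rate from the records before the PHP. And the ePJS audit is not conditioned on a repeat PHP, so it could cover people who do not return. The text uses it only for the timescale of actions.

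A reader might also infer more than the documents support:

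- *That a PHP with no effect would very likely still show increased uptake.* Step 2 shows this does not follow for a whole-group percentage on rolling items. The 11–45% range belongs to gap items only.
- *That the later RCT would be underpowered.* The article says the study will inform the RCT's design, not that the RCT will be sized on this change.
- *That national incentive schemes are pushing uptake up.* The Background says such schemes exist and that monitoring is inconsistent. It reports no rising trend.
- *That first and repeat percentages rest on different people.* A change by service users between two PHPs reads naturally as within-person. Pairing, intervals and missing-data handling may be set out in the full protocol, which is not shown, so their absence here is not a fault.

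**Conclusion.** The point holds as a mismatch between the aim and what the design can show. The Abstract (Background and Methods), the Background and the Discussion ask whether the PHP increases uptake or access. With no comparator, a change measured only in repeaters and an audit that starts at PHP completion, the pilot cannot answer that.

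The possible size depends on the reading. For actions on baseline gaps, closure with no PHP effect is illustratively 11–33% by 4 months and 16–45% by 6 months, assuming 30–70% annual uptake at a constant rate shared by everyone. For whole-group percentages on rolling items, no rise need occur from recurrence alone. Selective return could move the figure among repeaters well away from that for all first-PHP completers, by an amount the article gives no means of fixing.

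The textual mismatch is certain; the magnitudes are illustrations. It deserves a change because the remedy is cheap and alters what the pilot can conclude.

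**What to change.** 1. **Reword the aim** in the Abstract (Background and Methods), the Background and the Discussion: describe use, feasibility and observed change in uptake, and inform the RCT design. Leave effectiveness to the later trial, as the Discussion already does.
2. **Report audited uptake for everyone who completed a first PHP**, whether or not they repeat it. Beside it, give the first-to-repeat change in repeaters, counting both No→Yes and Yes→No, with 95% CIs.
3. **Optionally, extend the audit back** by a window before the first PHP equal in length to the window after it, for the same people. Cover all auditable items. For an item marked as not done in the past year, a 4–6 month look-back should contain almost no checks by construction, so a look-back limited to gap items would force an apparent rise. Exclude entries that exist only because the PHP was uploaded. Present the comparison as descriptive, because recording of checks may itself increase after the PHP: ePJS is the mental health trust's record, and the Background notes that sharing information with primary care is difficult.

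The cost is more work in records already being audited, consent wording to cover any look-back, and a more modest stated aim. Item 1 alone costs almost nothing.

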**Fig. 3 Fig3:**
[figure not shown]
PHP study schedule of enrolment and assessments

We will use the data gained from the study to understand the characteristics of the people who require more support in completing the PHP and the preferences for either the paper or digital versions. We will also capture data on how much training and which format was needed for successful implementation.

*Stage 3: Qualitative evaluation of the use of the PHP*

Interviews will be undertaken with a random selection of service users and clinical staff at the end of the study period. We do not have an estimate of how many people will engage with the PHP. Depending on uptake, we anticipate that 10–20% will be approached and invited to take part in the interview. We do not anticipate more than 20 interviews. The interviews will be semi-structured and ask questions to understand:Service user views on using the PHP and the actions they take after completing the PHPStaff views on the use of the PHP and the actions taken after the PHP is completedWhat, if any, problems were encountered in completing the PHP

We will attempt to contact service users who declined to complete the PHP to ask their reasons for not wanting to complete it. Informed consent will be obtained for all interviews.

### Patient and public involvement

Involving key stakeholders, particularly service users and clinical staff, is an important part of this project. In the pre-clinical and modelling phases, we involved service users as both facilitators and participants in focus groups and surveyed team leaders. We aim to work with some of the participants in the initial focus groups to help us to monitor and evaluate the project, by setting up a steering group which will meet six monthly over the period of the project and be involved in commenting on the findings of the study and making plans for future implementation. We will work with the steering group to devise a dissemination plan for participants.

### Analysis

#### Quantitative data

We will analyse the use of the PHP using the questions listed above and calculate numbers and percentages for each question. For the PAM and PHASe questionnaires, we will look at change in scores.

#### Qualitative data

We will analyse the interviews after the use of the PHP using thematic analysis to capture the main themes in the use of the PHP. Thematic analysis will be used as it is a method of analysing qualitative data that seeks to identify and make sense of any themes found in the data. We will follow the steps outlined by Braun and Clarke [28].

## Discussion

The information from the exploratory study will help us to understand how people use the PHP, what aspects of it are helpful, and how it is best used and implemented in individual teams and by individual service users. This will therefore help us in designing a larger trial to evaluate effectiveness and to be able to roll out the PHP for use across the Trust and wider across the NHS. People with SMI are known to have poorer physical health than the general population. This has become more widely acknowledged in recent years, and how to address this is a key question [29] with action needed at different levels from societal to individual. The PHP is one method developed to address this. This study aims to evaluate a service user-completed Physical health plan to find out if using it will increase access to physical health services. It is important to understand how new initiatives work at team level to understand if they can be implemented at scale. The use of a Theory of Change and the RE-AIM framework will help us to do this. We will use QI methodologies which will allow us to modify or amend the procedures if this is considered helpful by participants. We will work closely with service users and clinical staff to understand how it is used. This will also allow us to understand if the PHP can be implemented on a larger scale and inform the design of a large scale definitive RCT.

## Trial status

Protocol version number: 13, date: 09.02.2017, recruitment began: December 2017, recruitment will be completed: September 2019.

## Abbreviations

ePJS: Electronic Patient Journey System
IMPARTS: Integrating Mental and Physical Health: Research, Training and Services
KHP: King’s Health Partners
MRC: Medical Research Council
NICE: National Institute of Health and Care Excellence
PHP: Physical health plan
QI: Quality improvement
SLaM: South London and Maudsley NHS Foundation Trust
SMI: Serious mental illness
ToC: Theory of Change
WRAP: Wellness Recovery Action Plans
